#### Additional study parameters

2.8.4

Sex differences and the role of menopausal status in raloxifene efficacy will be explored with regard to the change in positive, negative, general and total symptoms (PANSS) between baseline, 6 weeks and 12 weeks of treatment and change in cognitive function (BACS) between baseline and 12 weeks. These analyses will be performed specifically in the group of patients that received raloxifene treatment, by means of repeated measures ANOVA with time as within factor gender and/or menopausal status as between factor. Furthermore, the analyses on other study parameters, including data from the follow-up visit (6 months after treatment), will be similar to the primary and secondary analyses. With regard to safety data, incidences of key SAEs and AEs will be presented per group. This includes the number and percentage of subjects with at least one occurrence of a SAE or AE. For exploratory purposes, confidence intervals comparing both groups will be provided.

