## Abstract

Although acute psychotic symptoms are often reduced by antipsychotic treatment, many patients with schizophrenia are impaired in daily functioning due to the persistence of negative and cognitive symptoms. Raloxifene, a Selective Estrogen Receptor Modulator (SERM) has been shown to be an effective adjunctive treatment in schizophrenia. Yet, there is a paucity in evidence for raloxifene efficacy in men and premenopausal women. We report the design of a study that aims to replicate earlier findings concerning the efficacy of raloxifene augmentation in reducing persisting symptoms and cognitive impairment in postmenopausal women, and to extend these findings to a male and peri/premenopausal population of patients with schizophrenia. The study is a multisite, placebo-controlled, double-blind, randomised clinical trial in approximately 110 adult men and women with schizophrenia. Participants are randomised 1:1 to adjunctive raloxifene 120 mg or placebo daily during 12 weeks. The treatment phase includes measurements at three time points (week 0, 6 and 12), followed by a follow-up period of two years. The primary outcome measure is change in symptom severity, as measured with the Positive and Negative Syndrome Scale (PANSS), and cognition, as measured with the Brief Assessment of Cognition in Schizophrenia (BACS). Secondary outcome measures include social functioning and quality of life. Genetic, hormonal and inflammatory biomarkers are measured to assess potential associations with treatment effects. If it becomes apparent that raloxifene reduces psychotic symptoms and/or improves cognition, social functioning and/or quality of life as compared to placebo, implementation of raloxifene in clinical psychiatric practice can be considered.

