#### Group assignment and masking

2.6.1

Randomisation is performed centrally at the Julius Center for Health Sciences and Primary Care, University Medical Center Utrecht. A web-based application with a minimisation procedure is used. Stratification is performed for gender, age and general functioning. The following people are blinded: participants receiving the treatment, persons administering the treatment, persons assessing the outcomes, persons analysing the data. Trial treatment randomisation codes are not available to the study staff, but are available at the local pharmacy for emergency unblinding.

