#### Primary study parameters

2.8.2

The primary analysis will include change in psychotic symptoms as measured by the PANSS at 6 and 12 weeks of treatment (end-of-treatment) and at 6 months after end of treatment and change in cognitive functioning as measured by the BACS at 12 weeks of treatment (end-of-treatment) and at 6 months after end of treatment. A mixed model for repeated measurements will be used, including at least time point, treatment group, the interaction between time point and treatment, sex and age as fixed factors, baseline PANSS/BACS-score, concomitant antipsychotic medication which will be converted to mean daily olanzapine equivalent dose [47], current drug and alcohol use as covariate and subject as random intercept factor. More specifically, the primary analysis will be a repeated measures analysis of variance (ANOVA) with time as within factor (baseline, 6 weeks and 12 weeks of treatment) and treatment as between factor (raloxifene or placebo), with symptom severity (PANSS total, positive, negative or general scores) as dependent variables. For the analysis of cognitive function, the BACS-scores of each of the six domains will be converted into six separate and a composite Z-score for each participant, controlling for age and gender [48]. Separate repeated measures ANOVAs will be performed for the separate *Z*-scores as dependent variables, time as within factor (baseline and 12 weeks of treatment) and treatment as between factor (raloxifene or placebo). The contrast between raloxifene and placebo at 6 and 12 weeks of treatment will be presented with a 95% confidence interval for the difference between the treatment arms. In addition, post-hoc analyses will be conducted to investigate differences at individual time points. There will be corrected for multiple testing by adjusting the p-values produced by each statistical test for each outcome using the Holm method [49,50].

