## Discussion

3

The attainment of full remission of symptoms is one of the major challenges in schizophrenia [6]. Despite current treatment options, diverse positive negative and cognitive symptoms of schizophrenia seem to be permanent and show no improvement over time [[4], [5], [6]]. This study investigates the potential efficacy of raloxifene in order to reduce these persistent symptoms and to improve treatment options for both men and women with schizophrenia. A previous meta-analysis by our group has shown raloxifene to be effective in reducing overall symptomatology [36], yet these findings are based on trials that included predominantly postmenopausal women. Furthermore, research suggests that raloxifene augmentation may be effective in improving cognition in postmenopausal women [26,27,31,33,51], and two trials have shown that this beneficial effect on cognitive functioning may also extend to men and premenopausal women [27,30]. However, the effects on cognition remain inconclusive till date [[33], [34], [35], [36]].

Therefore, we aim to elucidate whether the beneficial effects of raloxifene on positive, negative and cognitive symptoms can be replicated in postmenopausal women, and extrapolated to men and pre-and perimenopausal women with a schizophrenia spectrum disorder. We expect that raloxifene will lower symptom severity and improve cognition when compared to placebo. Furthermore, we expect to find increases in general and social functioning measures since these are highly related to negative symptoms and cognitive functioning [5], and a reduction of use of health and non-health resources.

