### Added value of this study

3.1

Based on the current literature, there is substantial evidence for the efficacy of raloxifene to reduce symptoms in postmenopausal women with schizophrenia. There is however a paucity in studies of raloxifene efficacy in men and premenopausal women. More evidence is needed to extrapolate its effectiveness and safety profile from this particular patient population towards the entire population of patients with schizophrenia. We therefore aim to replicate recent positive results by conducting a trial in which both men and women with schizophrenia receive raloxifene during 12 weeks in addition to their antipsychotic medication. If we are able to replicate previous positive findings, this evidence may facilitate implementation of raloxifene into general treatment for patients with schizophrenia.

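### The sex and menopause exploration uses the raloxifene arm alone, so it cannot separate differential drug effect from differential non-drug change

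*Protocol article*

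**What the plan says.** Section 2.8.4 (Additional study parameters) states the question: "Sex differences and the role of menopausal status in raloxifene efficacy will be explored", for PANSS change to weeks 6 and 12 and BACS change to week 12. It then fixes the population, "These analyses will be performed specifically in the group of patients that received raloxifene treatment", and the model, "by means of repeated measures ANOVA with time as within factor gender and/or menopausal status as between factor". No treatment factor appears.

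Section 2.8.2 describes the primary mixed model as "including at least time point, treatment group, the interaction between time point and treatment, sex and age as fixed factors". Sex is a main effect there, and time by treatment is the only interaction named.

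The abstract gives the trial's purpose as replication in postmenopausal women and then "to extend these findings to a male and peri/premenopausal population of patients with schizophrenia". The Discussion repeats it: the question is whether the benefits "can be replicated in postmenopausal women, and extrapolated to men and pre-and perimenopausal women with a schizophrenia spectrum disorder". Section 3.1 adds: "More evidence is needed to extrapolate its effectiveness and safety profile from this particular patient population towards the entire population of patients with schizophrenia".

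Section 2.6.1 says of the minimisation: "Stratification is performed for gender, age and general functioning".

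**The concern.** Section 2.1 defines effectiveness against placebo. A difference in efficacy between men and women is therefore a difference between two raloxifene-minus-placebo contrasts. The planned ANOVA contains neither contrast. It compares change over time between subgroups of treated patients, and that change includes whatever would have happened without the drug: illness course, placebo response, regression to the mean, and practice on the BACS.

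If any of these differs by sex or menopausal status, the test can report differential efficacy where there is none, or hide it where it exists. The Introduction describes marked sex differences in the course of the illness, so the possibility is not far-fetched. Even where non-drug change is the same in every subgroup, improvement within treated men or treated premenopausal women does not show that the drug caused it.

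At stake is the question that sets this trial apart from those done mainly in postmenopausal women. As written, it would be answered by a comparison that gives up the randomisation.

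**Working it through.** **The plan's own figure.** The article gives no figure for the subgroup analysis, only for the overall comparison (section 2.8.1: effect 0.57 SD, two-sided 5%, 80% power, 50 evaluable per arm). It reproduces: 2 × (1.960 + 0.842)² / 0.57² = 48.3, so 49 per arm by the normal formula. The t-test gives 49.3, so 50, with power 80.6%. The 50 evaluable per arm is used below.

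**What each analysis estimates.** Let g be the difference between the sexes in non-drug change, and d the difference between the sexes in drug effect.

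- Raloxifene arm only: difference in change = d + g.
- Placebo arm: difference in change = g.
- Treatment-by-sex interaction (first minus second) = d.

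If g = 0, the planned contrast equals d. Otherwise it is off by g.

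**Assumptions, none of them in the documents.** Change scores have SD 1. There are 50 evaluable patients per arm, split by sex either 25/25 or 38/12. The values of g are 0, 0.3 and 0.5 SD, and d = 0.

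**Standard errors.** The within-arm SE is √(1/a + 1/b); the interaction SE is √2 times that.

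- 25/25: √(2/25) = 0.283; interaction √(4/25) = 0.400.
- 38/12: √(1/38 + 1/12) = 0.331; interaction 0.468.

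**Chance that the raloxifene-only test is significant when d = 0** (two-sided 5%, noncentral t, 48 df, noncentrality g/SE):

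| g (SD) | 25/25 | 38/12 |
|---|---|---|
| 0 | 5% | 5% |
| 0.3 | 18% (0.3/0.283 = 1.06) | 14% (0.3/0.331 = 0.91) |
| 0.5 | 41% (0.5/0.283 = 1.77) | 32% (0.5/0.331 = 1.51) |

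A simulation of 20,000 trials at 25/25 agrees (5%, 18%, 41%). At g = 0.5 the rate is 41% whether the drug effect is 0.57 SD in both sexes or zero in both. The two-arm interaction test stays at about 5% throughout.

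**The opposite error.** With d = 0.57 and g = −0.57 the two cancel. In simulation the raloxifene-only test is significant in 5% of trials and the interaction test in 29%.

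**Precision of the interaction test.** For d = 0.57:

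- 25/25: 0.57/0.400 = 1.43, power about 29%.
- 38/12: 0.57/0.468 = 1.22, power about 23%.
- Detectable with 80% power: 2.80 × 0.400 = 1.12 SD, rising to 2.80 × 0.468 = 1.31 SD.

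**The case against.** Five points can be made for the plan.

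1. **The analysis is exploratory.** It stands under additional parameters, and the primary aim in section 2.1 names no subgroup. The primary analysis and the sample size rest on the overall placebo comparison. This stands, and it limits the severity. It excuses low power, but not a contrast that differs from the stated quantity.

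2. **The trial itself is sound.** A reader might infer that the trial cannot distinguish drug effect from natural course in these subgroups. The documents do not support that. Placebo patients are randomised 1:1, gender is a minimisation factor, and both arms follow the schedule in Table 1. They also remain in the primary and secondary analyses. Only this planned exploration omits them.

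3. **Non-drug change need not bias the contrast.** A reader might infer that practice effects or placebo response invalidate the comparison in themselves. They do so only if they differ between subgroups; equal amounts cancel. The contrast also contains any true difference in drug effect, so it is mixed rather than purely prognostic.

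4. **The documents give no size for g.** The Introduction speaks of course and symptom level, not of 12-week change on stable medication. The Discussion calls some residual symptoms seemingly permanent, which if anything suggests little non-drug change. The percentages are therefore conditional illustrations. A reader should not take 18% or 41% as this trial's error rate.

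5. **Section 2.8.2 lists its terms as a minimum,** so an interaction could be added. This helps little, because section 2.8.4 explicitly prescribes the single-arm method for this question.

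**Conclusion.** The point holds in a limited form and should be fixed. As written, section 2.8.4 estimates the difference in drug effect plus the difference in non-drug change and has no means of separating them. It is nevertheless the only specified analysis that addresses extension to men and pre/perimenopausal women. No section plans a raloxifene-placebo contrast by sex or menopausal status.

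The size depends on the unknown difference in non-drug change. There is no inflation if it is zero; at 0.3 to 0.5 SD the false-positive rate is 18% to 41% with an even sex split and 14% to 32% with 38/12. Those inputs, and the 50 evaluable raloxifene patients with equal drug effect in both sexes, are assumptions. No corresponding figure was worked out for menopausal status.

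It would go too far to conclude that the trial's efficacy result is compromised. The primary comparison with placebo is untouched, and the data needed for the right subgroup analysis are already being collected.

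**What to change.** Replace the raloxifene-only ANOVA in section 2.8.4 with an analysis of all randomised patients:

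- Add treatment-by-sex terms (with time) to the mixed model of section 2.8.2 and, among women, treatment-by-menopausal-status terms (with time).
- Report the raloxifene-minus-placebo difference at week 12 with its 95% confidence interval in men, in pre/perimenopausal women and in postmenopausal women.
- Keep the label exploratory.
- Delete the single-arm ANOVA, or keep it marked as descriptive only.

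The cost is a change of wording and a few model terms, with no extra patients, visits or assessments. The article reports recruitment as still open, so the change can be made before unblinding.

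The downside should be stated in the plan. The interaction SE is about 0.40 SD at an even sex split, against 0.28 SD for the single-arm contrast. Power for an interaction as large as the whole assumed effect (0.57 SD) is only about 23% to 29%, and an interaction of about 1.1 to 1.3 SD would be needed for 80% power. Menopausal status, analysed among women only, will be weaker still, and it is not a minimisation factor. The results should be read as estimates with intervals, not as proof of efficacy, or of its absence, in each subgroup.

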## Discussion

3

The attainment of full remission of symptoms is one of the major challenges in schizophrenia [6]. Despite current treatment options, diverse positive negative and cognitive symptoms of schizophrenia seem to be permanent and show no improvement over time [[4], [5], [6]]. This study investigates the potential efficacy of raloxifene in order to reduce these persistent symptoms and to improve treatment options for both men and women with schizophrenia. A previous meta-analysis by our group has shown raloxifene to be effective in reducing overall symptomatology [36], yet these findings are based on trials that included predominantly postmenopausal women. Furthermore, research suggests that raloxifene augmentation may be effective in improving cognition in postmenopausal women [26,27,31,33,51], and two trials have shown that this beneficial effect on cognitive functioning may also extend to men and premenopausal women [27,30]. However, the effects on cognition remain inconclusive till date [[33], [34], [35], [36]].

Therefore, we aim to elucidate whether the beneficial effects of raloxifene on positive, negative and cognitive symptoms can be replicated in postmenopausal women, and extrapolated to men and pre-and perimenopausal women with a schizophrenia spectrum disorder. We expect that raloxifene will lower symptom severity and improve cognition when compared to placebo. Furthermore, we expect to find increases in general and social functioning measures since these are highly related to negative symptoms and cognitive functioning [5], and a reduction of use of health and non-health resources.

In 2014, we performed a quantitative review and meta-analysis investigating hormone augmentation strategies in schizophrenia [24]. PubMed, Embase, PsycINFO and Cochrane Library databases were searched for augmentation with estrogens, selective estrogen receptor modulators (SERMs), testosterone, dehydroepiandrosterone (DHEA), pregnenolone and oxytocin in schizophrenia spectrum disorder. The search cut-off date was the last day of November 2014. Only publications on double-blind randomised placebo-controlled trials (RCTs) were included in our analyses. This search revealed that both estrogens and SERMs can be effective strategies for symptom reduction in postmenopausal women with schizophrenia. The SERM raloxifene was shown to have the best side effect profile. Furthermore, raloxifene is currently the only SERM approved for long-term treatment. Kulkarni performed an effective therapeutic dose study [25] for raloxifene augmentation, revealing that a dosage of 120 mg/day was more effective in improving symptomatology than the standard treatment dose of 60 mg/day [25].

In 2018, we performed a quantitative review and meta-analysis investigating raloxifene augmentation in schizophrenia [36], with a search cut-off date of October 2017. A systematic search was performed using PubMed (Medline), Embase, PsychInfo, and Cochrane Database of Systematic Reviews. RCTs investigating the effect of raloxifene in schizophrenia spectrum disorders were included in the quantitative analyses. Outcome measures were psychotic symptom severity, depression and cognition. Nine studies were included, investigating 561 patients with a schizophrenia spectrum disorder. Premenopausal women were included in one study [30], and men were included in two of these studies [29,30]. Raloxifene was superior to placebo in improving total symptom severity (ES = 0.57), as well as positive (ES = 0.32), negative (ES = 0.40), and general symptoms (ES = 0.46). No significant effects of raloxifene were found on cognitive function, although only a small number of studies could be included in these analyses (ranging from 2 to 4 studies for each cognitive domain). These studies included patients that were more severely ill [26,34,35,37], while it has been suggested that greater symptom severity might interfere with improvements in cognitive functioning [52]. Furthermore, a recent study in women with schizophrenia revealed that raloxifene treatment altered performance on specific cognitive domains, dependent on menopause status [27].

### Added value of this study

3.1

Based on the current literature, there is substantial evidence for the efficacy of raloxifene to reduce symptoms in postmenopausal women with schizophrenia. There is however a paucity in studies of raloxifene efficacy in men and premenopausal women. More evidence is needed to extrapolate its effectiveness and safety profile from this particular patient population towards the entire population of patients with schizophrenia. We therefore aim to replicate recent positive results by conducting a trial in which both men and women with schizophrenia receive raloxifene during 12 weeks in addition to their antipsychotic medication. If we are able to replicate previous positive findings, this evidence may facilitate implementation of raloxifene into general treatment for patients with schizophrenia.

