### Study population and eligibility criteria

2.4

A total of 110 men and women with schizophrenia, schizoaffective or schizophreniform disorder, or psychotic disorder not otherwise specified (NOS) will be included. Recruitment takes place in both in- and outpatient facilities throughout the Netherlands (Institute for Mental Health Care Eindhoven (GGzE), Eindhoven; Psychiatric Center Geestelijke Gezondheidszorg Centraal (GGz Centraal), Amersfoort; UMCU, Utrecht; Reinier van Arkel Institute for Mental Health Care (RvA), ‘s-Hertogenbosch), and one clinic in Belgium (Ziekenhuis Netwerk Antwerpen, ZNA, Antwerp). Patients are approached by their treating psychiatrist and informed about the study by the multidisciplinary study team.

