#### Power and sample size calculation

2.8.1

For the sample size calculation, a medium effect size of 0.57 was assumed, which is similar to the effect size for symptom severity detected in the most recent meta-analysis and the effect size for cognition [36,37]. Sample size calculation was based on disjunctive power (or minimal power), which is the probability of finding at least one true intervention effect across all of the outcomes. To be able to find an effect size of 0.57, with two sided alpha set at 5% and with 80% power, 50 participants in each group have to be evaluated. Since we expect some 10% dropout, a total of 55 participants per arm are needed, resulting in a total of 110 participants.

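### The stated goal of extending efficacy to men and pre/perimenopausal women is not matched by any planned raloxifene-placebo comparison in those groups; the 80% power covers the pooled contrast only

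*Protocol article*

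**What the plan says.** **Aim.** Section 2.1 words the primary aim for the whole sample: raloxifene against placebo on symptoms and cognition. The abstract and Discussion frame the purpose by population. The Discussion asks whether benefit "can be replicated in postmenopausal women, and extrapolated to men and pre-and perimenopausal women with a schizophrenia spectrum disorder". The Introduction says that existing benefits cannot be carried over to premenopausal women or men without further testing.

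**Size.** Section 2.8.1 states that "a medium effect size of 0.57 was assumed" and that "with two sided alpha set at 5% and with 80% power, 50 participants in each group have to be evaluated". Section 2.4 enrols one pool: "A total of 110 men and women with schizophrenia, schizoaffective or schizophreniform disorder, or psychotic disorder not otherwise specified (NOS) will be included". The article gives no number by sex or menopausal status.

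**Analysis.** The primary model in section 2.8.2 includes sex as a fixed factor and names no interaction of treatment with sex or menopausal status. Section 2.8.4 explores both characteristics, but only among patients who received raloxifene.

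**Conclusion.** Section 3.1 says "If we are able to replicate previous positive findings, this evidence may facilitate implementation of raloxifene into general treatment for patients with schizophrenia". The abstract likewise links a positive result to use in psychiatric practice. Neither statement is limited to a patient group.

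**The concern.** Section 3.1 already regards the evidence in postmenopausal women as substantial, so the open question is whether raloxifene works in men and in pre/perimenopausal women. A pooled test answers a different question: whether the average effect over the enrolled mix differs from zero. It cannot separate a benefit shared by all groups from one carried by postmenopausal women.

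The subgroup work does not fill the gap. Comparing change from baseline between men and women who all took raloxifene mixes drug effect with placebo response, practice effects on the BACS and natural course, each of which may differ by sex or age. Only a comparison with placebo patients of the same group isolates the drug effect.

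At stake is the claim the trial was set up to inform. A pooled positive could be taken as support for use in groups where no effect was estimated, and a flat result in one group would be hard to interpret at the numbers available.

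**Working it through.** **Inputs from the article.** Two-sided alpha 0.05, effect size d = 0.57, 50 evaluable per arm (section 2.8.1); 1:1 allocation (abstract).

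**Assumptions.** The mix is not given, so I use 10, 17, 25 and 35 evaluable patients per arm in a group (17 corresponds to equal thirds), balanced between arms. Tests are unadjusted two-sample t-tests.

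**Step 1: reproduce the plan's figure.** Noncentrality = d / √(2/n) = 0.57 / √(2/50) = 0.57 / 0.20 = 2.85. With 98 degrees of freedom, power is 80.6%, and 50 is the smallest n per arm that reaches 80%. Adding 10% gives 50 × 1.10 = 55 per arm, 110 in all. The figure is correct as a pooled contrast.

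**Step 2: the same calculation within one group.** The standard error in SD units is √(2/n). The 95% CI half-width is the t quantile times that.

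| Evaluable per arm in the group | Noncentrality | Power at 0.57 | Effect detectable with 80% power | 95% CI half-width (SD units) |
|---|---|---|---|---|
| 10 | 1.27 | 23% | 1.32 | 0.94 |
| 17 | 1.66 | 36% | 0.99 | 0.70 |
| 25 | 2.02 | 51% | 0.81 | 0.57 |
| 35 | 2.38 | 65% | 0.68 | 0.48 |
| 50 (pooled) | 2.85 | 81% | 0.57 | 0.40 |

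**Step 3: what a pooled positive can mean.** Suppose the effect is 0.57 in postmenopausal women and zero in everyone else. The average effect is 0.57 × f, where f is their share of the sample.

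| Share f | Average effect | Noncentrality (÷ 0.20) | Chance the pooled test is significant |
|---|---|---|---|
| 0.33 | 0.188 | 0.94 | 15% |
| 0.50 | 0.285 | 1.42 | 29% |
| 0.67 | 0.382 | 1.91 | 47% |

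These are power figures for a true, non-zero average effect. They show that a pooled positive is compatible with no effect outside postmenopausal women.

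**Step 4: a direct test of difference between groups.** For two groups with shares f and 1 − f, the standard error of the interaction is √(2/(50f) + 2/(50(1 − f))). At f = 0.5 this is √(0.08 + 0.08) = 0.40. Power to detect 0.57 against 0 is then about 30%; at a 20/80 split (standard error 0.50) it is about 21%. Treatment-by-group terms are therefore useful for estimation and weak as tests.

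**Step 5: what section 2.8.4 can estimate.** Within the raloxifene arm, the contrast is change in one group on raloxifene minus change in another group on raloxifene. No placebo patient enters, so the raloxifene-placebo difference cannot be recovered for any group, whatever the sample size.

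**The case against.** A reader might infer that the plan declares efficacy in men and premenopausal women whenever the pooled test is positive. The text does not support that. No section sets such a rule, the concluding sentences are conditional and hedged, and the sentence in section 3.1 speaks of replicating earlier findings without naming the pooled test.

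A reader might also set the 15% to 47% against a nominal 5% and call it inflated type I error. It is not: with an effect in part of the sample the pooled null is false, and rejecting it is correct.

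Further points in the plan's favour stand:

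- The formal primary aim in section 2.1 matches the powered contrast, and the subgroup work is described as exploratory. Low power in an exploratory subgroup is ordinary and no fault in itself.
- Randomisation accounts for sex and age, which helps balance within groups.
- The Introduction cites two trials in men and/or pre/perimenopausal women with positive effects, so exactly zero effect outside postmenopausal women is an illustration and not a prediction.
- Section 2.8.2 adjusts for baseline. If 0.57 is in raw SD units and the baseline correlation is 0.6 (both assumed), 17 and 25 per arm give about 52% and 69% instead of 36% and 51%.
- Expected numbers by group may be in the full protocol, so their absence from an article is not a fault.

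None of this supplies a placebo-controlled estimate by sex or menopausal status. Section 2.8.4 states which patients its analysis uses, and they are the raloxifene patients only. The hedging softens how strongly the conclusion is put but does not narrow the population it covers.

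**Conclusion.** The point holds as a mismatch between the population-specific purpose in the abstract and Discussion and the analyses described. The sample size is correct for what it covers, the pooled contrast. The planned analyses cannot support a claim of extension to men or pre/perimenopausal women, because none of those described compares raloxifene with placebo in those groups.

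The size depends on an unstated mix. Over 10 to 35 evaluable patients per arm in a group, unadjusted power at 0.57 runs from about 23% to 65%, and baseline adjustment would raise it. A pooled positive would arise in about 15% to 47% of trials with an effect confined to postmenopausal women at one third to two thirds of the sample. The conclusion about section 2.8.4 rests on no numerical assumption.

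**What to change.** 1. **Section 2.8.4:** use both arms. Add treatment-by-group terms to the primary model and report the raloxifene-placebo difference with its 95% CI for men, pre/perimenopausal women and postmenopausal women. Label this as estimation with limited precision.
2. **Section 2.8.1:** state that the 80% applies to the pooled sample. Adding expected precision or power by group would be optional reporting.
3. **Abstract, section 3 and section 3.1:** say that a pooled positive supports an average effect in the mixed sample. Claim replication or extension for a group only where that group's own estimate supports it; otherwise report the question as unresolved and do not read a non-significant group result as absence of effect.

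**Cost:** wording and a few extra model terms. No more patients or measurements are needed: sex is known, and menses, FSH and 17β-estradiol are already recorded at baseline to classify menopausal status. The article describes recruitment as still under way, so the change could be fixed before unblinding. The downside is wide group intervals (half-width roughly 0.5 to 0.9 SD, unadjusted) and a narrower claim.
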